### Ethical Considerations

This study was approved by the Ethics Committee of the Public Health Faculty (number: 1549/UN4.14.1/TP.01.02/2024). All participants were informed about the study’s purpose, procedures, potential risks, and right to withdraw at any time before data collection. Written informed consent was obtained after that. Initial screening for heavy metal exposure was conducted after informed consent was obtained. All historically collected data will be deidentified before the analyses. The participants received the equivalent of around US $6.25 for compensation.

### Research Procedure

#### Overview

The research step is presented in Figure 1.

**Figure 1. F1:**
[figure not shown]
Research step. Fe: ferrum (iron supplement); Hg: mercury; Pb: plumbum (lead); Cd: cadmium; 8-OHdG: 8-hydroxy-2'-deoxyguanosine; MDA: malondialdehyde.

#### Data Collection

An interview has been conducted with pregnant women using a questionnaire that contained questions about their characteristics and potential exposure sources. Data on food/supplement intake will also be obtained using a 24-hour recall form and a Food Frequency Questionnaire (FFQ) to assess exposure to heavy metals through food. Each participant provided 10 mL of venous blood sample, acquired using a tube lined with ethylenediaminetetraacetic acid (EDTA) and kept at a temperature of 2‐8 °C until analysis. For MDA and 8-OHdG analyses, blood samples were centrifuged to obtain plasma and stored at temperatures of −80 °C until analysis.

Heavy metals, 8-OHdG, and MDA concentrations as the outcomes will be measured at 2 time points: baseline (preintervention) and postintervention (after 8 weeks). The measurements at baseline will be performed at enrollment, before the administration of *M. oleifera* supplementation. The measurements at postintervention (after 8 weeks) will be performed at the end of the 2-month supplementation period, when the same biomarkers (blood heavy metals, 8-OHdG, MDA) will be reassessed to evaluate changes.

### Intervention Group

In addition to receiving iron capsules, which are standard supplements provided by the health centers as part of the national prenatal care program, participants in the intervention group also received *M. oleifera* extract supplementation at a dose of 2000 mg/day, administered as 2 capsules taken twice daily (totaling 2000 mg/day) for a continuous period of 8 weeks. Supplementation began immediately upon enrollment, which occurred between gestational weeks 20 and 32. Therefore, the regimen lasted from the time of enrollment until 8 weeks later, typically ending between weeks 28 and 40 of gestation. For participants enrolled in the late third trimester who delivered before completing the full 8 weeks, they were instructed to continue consuming the remaining *M. oleifera* supplements until the full course was completed. This approach aimed to ensure consistency in the intervention dosage, regardless of the timing of delivery, and to maintain the study’s internal validity.

To support adherence, we collaborated with health cadres at each participating health center. The cadres will be responsible for supervising, reminding, and ensuring that the mothers consistently take the moringa capsules. A WhatsApp group was established specifically for the cadres to facilitate regular communication, provide reminders, and monitor the supervision process throughout the 8-week supplementation period. We have also added a simple adherence log that will be maintained by the cadres, documenting capsule intake daily based on direct questioning or observation. These dual approaches—cadre monitoring and pill counts—will allow us to triangulate adherence data and better distinguish true intervention effects from variability due to compliance.

Participants will be actively monitored for adverse events throughout the 8-week intervention period. At the follow-up visit, participants will be asked about any symptoms or side effects experienced, using a structured checklist and open-ended questions. Specific adverse events of interest include gastrointestinal discomfort (nausea, vomiting, and diarrhea), allergic reactions (skin rash and swelling), and general intolerance to the supplement.

Any serious adverse events, including pregnancy complications such as preeclampsia, gestational diabetes, preterm labor, or hospitalizations, will be recorded and reviewed by the study physician. Although these are not primary outcomes, maternal and fetal complications will be documented to ensure a complete safety profile.

Prior evidence suggests that *M. oleifera* supplementation at a dose of 2000 mg/day is safe for human use, including during pregnancy. However, all safety data will be recorded in participant case report forms, monitored by the study team, and summarized in the final report.

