#### Capsule Supplement Production

The dry extract was ground again using mesh 100 to obtain a fine extract powder. This powder was then mixed with corn starch as a filler in a 4:1 ratio (400 mg of moringa extract and 100 mg of corn starch per capsule). Each capsule contained 400 mg of moringa leaf extract. Participants in the intervention group received 2 capsules twice daily (totaling 2000 mg/d) for a period of 8 weeks, beginning immediately upon enrollment (between gestational weeks 20‐32). In cases where participants gave birth before completing the 2-month supplementation period, they were instructed to continue consuming the remaining *M. oleifera* supplements until the full course was completed. This approach aimed to ensure consistency in the intervention dosage, regardless of the timing of delivery, and to maintain the study’s internal validity.

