#### Quality Control

After production, supplementation with moringa leaf extract capsules was tested to ensure weight uniformity and quality, including checks for moisture content, microbial presence, and organoleptic tests to ensure product safety and quality. The dosage of moringa leaf supplementation in this study was determined based on several previous safety studies [34-36], which indicated that the consumption of moringa leaves is safe at doses up to 2000 mg/day for humans and has the potential to be a safe source of antioxidants for pregnant women.

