While the study aims to demonstrate reductions in blood heavy metals and oxidative stress biomarkers following *M. oleifera* supplementation, such findings—if observed—should be interpreted with caution. Positive outcomes would indicate that moringa is a promising candidate for reducing biochemical risk factors associated with environmental exposures in pregnancy. However, this study does not assess long-term or clinical outcomes (eg, fetal growth and birth weight) and therefore cannot confirm improvements in maternal or fetal health. Additionally, the study does not evaluate cost-effectiveness or scalability of implementation.

Conversely, if no significant effects are observed, several factors could explain this, including insufficient dosage, short intervention duration, limited sample size, or individual variability in absorption or baseline exposure. These considerations will guide future study design and refinement of the intervention strategy. Ultimately, findings from this study should be viewed as hypothesis-generating, laying the groundwork for larger, randomized trials with extended follow-up and clinical endpoints.

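### The extract dose is stated as 2000 mg/day, but the capsules described supply 1600 mg/day of extract; 2000 mg/day is the fill weight including corn starch

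*Protocol article*

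**What the plan says.** The Capsule Supplement Production section states that the dry extract was mixed with filler in a 4:1 ratio, specified as "400 mg of moringa extract and 100 mg of corn starch per capsule". It then repeats the active content: "Each capsule contained 400 mg of moringa leaf extract". The next sentence says that intervention participants "received 2 capsules twice daily (totaling 2000 mg/d) for a period of 8 weeks".

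The Intervention Group section describes the same regimen as "extract supplementation at a dose of 2000 mg/day, administered as 2 capsules taken twice daily", again with a bracketed total of 2000 mg/day.

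The figure of 2000 mg/day also appears where the article cites earlier work. The Quality Control section says that "consumption of moringa leaves is safe at doses up to 2000 mg/day for humans". Later, the Intervention Group section says that "supplementation at a dose of 2000 mg/day is safe for human use, including during pregnancy". The Safety and Tolerability section expects this trial's safety profile to agree with earlier studies at that dose.

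Nowhere does the text give 1600 mg/day, or say that 2000 mg/day includes the starch.

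**The concern.** The two Methods sections cannot both be right about the extract. One fixes 400 mg of extract per capsule and four capsules a day. The other gives a daily extract dose that four such capsules cannot supply. Someone who reads only the Intervention Group section would record 2000 mg of extract per day as the exposure under test.

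The dose matters in three places:

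- **Efficacy.** Any effect on blood metals, 8-OHdG or MDA will be attributed to the dose as reported.
- **A null result.** The Principal Anticipated Findings section says that, with no significant effect, "several factors could explain this, including insufficient dosage, short intervention duration, limited sample size" and that these considerations will guide refinement of the intervention. Judging whether the dose was too low requires the dose actually supplied.
- **Safety.** If this trial's exposure is reported as 2000 mg/day of extract, it will be credited with tolerability in pregnant women at an extract dose higher than the one taken.

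**Working it through.** **Inputs**

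| Quantity | Value | Source |
|---|---|---|
| Extract per capsule | 400 mg (stated twice) | Capsule Supplement Production |
| Corn starch per capsule | 100 mg | Capsule Supplement Production |
| Extract-to-starch ratio | 4:1 | Capsule Supplement Production |
| Capsules per day | 2 × 2 = 4 | Capsule Supplement Production; Intervention Group |
| Duration | 8 weeks = 56 days | Both sections |
| Stated extract dose | 2000 mg/day | Intervention Group |

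**Step 1: reproduce the plan's figure.** Daily mass = capsules per day × mass per capsule.

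- Total fill: 4 × (400 + 100) = 4 × 500 = 2000 mg/day. This matches.
- Extract only: 4 × 400 = 1600 mg/day. This does not match.
- Starch only: 4 × 100 = 400 mg/day.

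Only the fill weight, starch included, gives 2000 mg/day.

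**Step 2: cross-check from the ratio.** At 4:1, extract makes up 4/5 of the fill: 2000 × 4/5 = 1600 mg/day. This agrees with Step 1.

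**Step 3: size of the discrepancy.**

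- Relative to the stated dose: (2000 − 1600)/2000 = 20% lower.
- Relative to the dose supplied: 2000/1600 − 1 = 25% overstated.
- Over the full course: 56 × 4 = 224 capsules. Extract supplied is 224 × 400 mg = 89.6 g, against an implied 56 × 2000 mg = 112.0 g. The gap of 22.4 g equals the starch, 224 × 100 mg.

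**Step 4: what 2000 mg/day of extract would take.** Either 2000/4 = 500 mg of extract per capsule at four capsules a day, or 2000/400 = 5 capsules a day at the stated content. The article describes neither.

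**The case against.** The best reply is that the authors multiplied correctly and 2000 mg/day simply means capsule mass. In the Capsule Supplement Production section that is the natural reading, because the composition is given just before the daily total. The true extract content is also fully disclosed there, so anyone following that section would make the right capsule and give the right number. Adherence is tracked by capsule logs and pill counts, no analysis uses the milligram figure, and the trial has a single fixed dose. On this view a few words of labelling are at stake.

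Much of this stands. It is why the finding is confined to labelling and reporting, and why the production section needs only a clarifying word if its composition is right. It does not rescue the Intervention Group section, where the dose is attached directly to the extract. Nor does the condensed format of an article explain it: both figures are given and they conflict, and a fuller document could only show which one to correct.

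One further point is fair. The safety bound in the Quality Control section is worded for moringa leaves, while the capsules hold a freeze-dried aqueous extract, and the article gives no extraction yield. Milligrams of extract therefore cannot be set against that bound, either to reassure or to alarm. The finding does not depend on that comparison.

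**Conclusion.** The concern holds. As written, the Intervention Group section overstates the daily extract dose: the capsules described supply 1600 mg/day, 20% below the stated 2000 mg/day.

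This rests on the stated composition of 400 mg extract plus 100 mg starch being correct. The support within the article is good: the 400 mg is given twice, it agrees with the 4:1 ratio, and the resulting 500 mg fill reproduces 2000 mg/day exactly. The production records were not available to confirm it, and neither was Figure 1. The course totals also assume full adherence.

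The point should be fixed, but it does not undermine the design. The regimen in capsules, the sample size and the between-group analysis are unaffected. The 2000 mg/day that the article attributes to earlier studies is not made wrong by this, and nothing here shows a safety limit exceeded.

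**What to change.** 1. Check the production records for the extract content per capsule.
2. If 400 mg is confirmed, restate the dose in the Intervention Group section as 1600 mg/day of extract (2000 mg/day of capsule fill), and label the daily total in the Capsule Supplement Production section as fill weight.
3. If the records show 500 mg of extract per capsule, correct the composition in the Capsule Supplement Production section instead.
4. In the results paper, and in any safety conclusion drawn from this trial, name the exposure as the confirmed extract dose: 1600 mg/day if step 2 applies.
5. Leave unchanged the 2000 mg/day attributed to earlier studies in the Quality Control, Intervention Group and Safety and Tolerability sections.

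The cost is a records check and a few words in two Methods sections. Design and analysis stay as they are.

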## Methods

### Study Design

This study is an ongoing quasi-experimental investigation that uses a nonrandomized pre-post test methodology. Expectant mothers were divided into 2 cohorts, one receiving an intervention and the other serving as a control. This study applied a nonrandomized pre-post test design due to practical considerations related to (1) practical management, (2) geographical differences, and (3) time constraints.

First, practical management considers that managing the study is easier when specific locations are designated for the intervention group and other locations for the control group. This approach ensures that the intervention (*M. oleifera* supplementation) can be efficiently delivered and monitored in each location without the complexity of randomizing participants across multiple sites. Furthermore, grouping participants by location helps streamline logistical operations such as monitoring compliance and ensuring consistent follow-up over the course of the intervention period.

Second, although the geographical settings of the intervention and control groups may differ, they were comparable in terms of demographic characteristics and environmental conditions. This allowed us to evaluate the effects of moringa supplementation in different geographical settings while maintaining comparability between groups. In addition, by focusing on distinct locations for intervention and control, we ensure better resource allocation and minimize the logistical challenges that would arise from attempting to randomize participants across a broader region.

Third, time was considered a constraint due to limitation in the laboratory. We could not receive heavy metal analysis results from the initial screening at the same time for all participants. Therefore, women with high levels of heavy metals at the first screening were included in the intervention group to avoid delays. This ensures that these participants can begin the 2-month intervention with *M. oleifera* as soon as possible after obtaining the result, considering the limited research timeframe. Furthermore, because we limited the overall time for the study, randomizing participants could cause delays in implementing the intervention and complicate the process of ensuring that those with high levels of heavy metals receive timely treatment.

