The required sample size was calculated using an estimated effect size (Cohen *d*) of 0.42, derived from a previous intervention study in South Sulawesi, which assessed the effects of *M. oleifera* supplementation on oxidative stress biomarkers in pregnant women exposed to passive smoking [37]. The study reported a mean difference in 8-OHdG levels between treatment groups of approximately 12.96 ng/mL with a pooled SD of ~30.68 ng/mL, yielding a moderate effect size. Using a 1-sided test with *α*=.05 and 80% power, the minimum required sample size is 37 participants per group. To account for an anticipated 20% dropout rate, the sample size was increased to 44 participants per group, yielding a total of 88 participants.

Approximately 200 pregnant women attending routine antenatal care (ANC) visits at the community health centers were sequentially approached and invited to participate in the study. They were first interviewed to determine eligibility based on inclusion and exclusion criteria. Those meeting the criteria were provided with detailed information about the study and asked to provide written informed consent. Following consent, a blood sample was collected to assess baseline levels of heavy metals.

Only participants with elevated levels above reference thresholds were considered eligible for inclusion in the intervention phase. For the intervention group, eligible participants were contacted and provided with *M. oleifera* supplements along with instructions for daily consumption over a 2-month period. They were informed that a follow-up blood collection would occur at the end of the supplementation period during a routine visit.

For comparison, the control group was recruited from a different health center in a separate subdistrict administrative unit that did not receive moringa supplementation. This approach minimized contamination between groups and allowed for feasible implementation of the intervention. Follow-up blood sampling was also conducted after 2 months, aligned with their next scheduled antenatal visit, but without providing moringa supplementation.

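### Baseline blood precedes the metal result and capsules follow it, so the moringa arm's pre-post interval is 8 weeks plus an unstated laboratory delay, and the start of the controls' 2 months is not defined

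*Protocol article*

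**What the plan says.** Two accounts of the timing stand in the Methods.

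*Enrollment as one moment.* Data Collection says of the biomarkers that "The measurements at baseline will be performed at enrollment, before the administration of" the supplement. Intervention Group says "Supplementation began immediately upon enrollment, which occurred between gestational weeks 20 and 32", with the course typically ending at weeks 28 to 40; Capsule Supplement Production gives the same start. Data Collection allows two measurement times only, before the intervention and after 8 weeks, and ties the second to the end of the 2-month course.

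*A sequence with a wait in it.* Participant Recruitment says "Following consent, a blood sample was collected to assess baseline levels of heavy metals", then "Only participants with elevated levels above reference thresholds were considered eligible for inclusion in the intervention phase", and for the intervention arm "eligible participants were contacted and provided with" the capsules. Study Design says "We could not receive heavy metal analysis results from the initial screening at the same time for all participants", and that the course was to begin "as soon as possible after obtaining the result".

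For controls, Participant Recruitment says only this: "Follow-up blood sampling was also conducted after 2 months, aligned with their next scheduled antenatal visit". The event from which those 2 months are counted is not given. An elevated metal level is an inclusion criterion for both groups.

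The between-group analysis (Data Analysis) is a difference-in-differences with ANCOVA. The covariates it names are maternal age, gestational age, education level and baseline biomarker levels.

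**The concern.** A draw made at consent, an assay that must come back before eligibility is known, and capsules that start after the result cannot share one moment with the baseline measurement unless the delay is nil or a fresh sample is taken before the first capsule. The article describes no fresh sample. It also names a laboratory limitation as a reason for not randomizing, which makes a nil delay hard to assume.

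A difference-in-differences estimate credits to moringa whatever extra change the intervention arm shows. That is fair only if both arms are watched over a similar span. If one arm is watched longer, its estimate also carries more of the change that pregnancy brings regardless of treatment. Adjusting for gestational age as a baseline variable does not capture the time that passes between the two draws.

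**Working it through.** **Inputs.** Course length 8 weeks and enrollment at weeks 20 to 32 (Intervention Group). Follow-up at the end of the course (Data Collection). Control follow-up after 2 months (Participant Recruitment), taken as 8.0 weeks, or as 60.875 / 7 = 8.7 weeks if calendar months are meant. L is the time from baseline draw to first capsule; it is not stated, and the range 0 to 8 weeks is my assumption.

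**Step 1: the article's own figure.** 20 + 8 = 28 and 32 + 8 = 40, so weeks 28 to 40 reproduce exactly, with L = 0 or with enrollment meaning the first capsule.

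**Step 2: what enrollment can mean.**
- If it is the blood draw, the course ends at weeks 28 + L to 40 + L. With L = 4 that is weeks 32 to 44, against the stated 28 to 40.
- If it is the first capsule, the baseline blood dates from weeks 20 − L to 32 − L. With L = 4 that is weeks 16 to 28, against the statement that baseline is measured at enrollment.

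Either way the moringa-arm interval between draws is L + 8 weeks.

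**Step 3: gap between arms (moringa minus control).**

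| L (weeks, assumed) | Moringa interval, L + 8 | Gap if controls count from the draw (8.7 to 8.0 weeks) | Gap if controls count from the result, same L |
|---|---|---|---|
| 0 | 8 | −0.7 to 0 | −0.7 to 0 |
| 1 | 9 | 0.3 to 1 | −0.7 to 0 |
| 2 | 10 | 1.3 to 2 | −0.7 to 0 |
| 4 | 12 | 3.3 to 4 | −0.7 to 0 |
| 8 | 16 | 7.3 to 8 | −0.7 to 0 |

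If controls count from the result but the delay differs by arm, the gap is L(moringa) − L(control), less up to 0.7 weeks.

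**Step 4: what a gap could do (illustration only).** The Introduction gives early and late pregnancy averages from a cited birth-weight study. I assume linear change and 20 weeks between the two measurements; the article gives neither.

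| Metal | Early to late | Change | Per week (÷ 20) | Over a 4-week gap |
|---|---|---|---|---|
| Hg (μg/L) | 2.37 to 1.95 | −0.42 (−17.7%) | −0.021 | −0.084 (−3.5%) |
| Pb (μg/dL) | 0.74 to 0.70 | −0.04 (−5.4%) | −0.002 | −0.008 (−1.1%) |
| Cd (μg/L) | 0.62 to 0.70 | +0.08 (+12.9%) | +0.004 | +0.016 (+2.6%) |

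Percentages are of the early value. For gaps of 2 and 8 weeks, the Hg figure is −0.042 (−1.8%) and −0.168 (−7.1%). A longer moringa interval would flatter the supplement for Hg and slightly for Pb, and count against it for Cd. The article gives no early and late values for 8-OHdG or MDA, so no such sum can be done for them.

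**The case against.** The strongest reply is that enrollment may mean confirmed eligibility. That fits the inclusion criterion on metal levels, and then the immediate start, weeks 20 to 32 and weeks 28 to 40 all agree with the recruitment account. Only the statement that baseline is measured at enrollment is loose. This is fair, but that statement is the one that matters here: the moringa-arm interval is L + 8 weeks under either meaning.

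A reader might go further and infer that controls were definitely observed for a shorter time, so that moringa is credited with a spurious fall. The article does not support that. It never says when the controls' 2 months start. Controls also had to have an elevated result, so their clock may have started there. Intervention follow-up was likewise at a routine visit, so tying samples to visits is not peculiar to controls. Counting from the draw is the more natural reading, because controls have no capsule start, but it is not proven. Nor does the article say that results came late, only that they did not all come at once.

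It is also fair that the drift illustration borrows another cohort's averages, that the Pb effect is about 1% at a 4-week gap, and that the Cd effect runs against the supplement. The covariate list is introduced as examples, so elapsed time is not ruled out. Figure 1, which sets out the research steps, was not available for this check. A fresh pre-capsule sample shown there would reduce the point to one of wording.

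**Conclusion.** The concern holds in a limited form. Study Design and Participant Recruitment conflict with Data Collection, Intervention Group and Capsule Supplement Production on when baseline and first capsule occur. As described, the moringa-arm pre-post interval is 8 weeks plus an unstated delay that varies between women, not 8 weeks. This rests on the baseline sample being the screening sample, as the article says, and on no second pre-capsule draw.

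An imbalance between arms is possible but not established. It ranges from about zero to about L weeks, depending on a control starting point that the article leaves open and on whether the delay was alike in both arms. If a gap exists, none of the named covariates removes it, and it biases the between-group estimates by an amount and in a direction that differ by metal. No single figure can be fixed without L.

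**What to change.** 1. Reconcile Study Design, Participant Recruitment, Data Collection, Capsule Supplement Production and Intervention Group. Define enrollment, say whether any second sample preceded the first capsule, and name the event that starts the follow-up clock in each arm.
2. For women still to be sampled, use the same event and the same window in both arms. Some samples may then not coincide with a routine visit. This aligns the rule but does not equalize the interval if the laboratory delay itself differs by arm, so step 3 is needed too.
3. For all women, derive weeks from baseline draw to follow-up draw, show the distribution by arm, and add it as a covariate or sensitivity analysis in the difference-in-differences and ANCOVA models. Record the dates of baseline draw, result, first capsule and follow-up draw where they can be recovered.

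The cost is protocol wording, one derived variable and some precision. If the interval overlaps little between arms, the covariate cannot fully separate elapsed time from treatment, and this should be stated as a limitation. Laboratory work on the second step was already under way in February 2025, so step 2 may reach few women; steps 1 and 3 remain possible for all.
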